## Abstract

**Background:**

The mental wellbeing implications of a prostate cancer diagnosis are increasingly being realised. Significant mental health symptoms such as depression and anxiety, along with related constructs such as fear of cancer recurrence, body image and masculine self-esteem issues are prevalent. However, less is understood about potential prognostic factors for these outcomes in prostate cancer patients. Therefore, this study aims to primarily explore potential treatment, patient and oncological factors associated with mental wellbeing outcomes in the initial prostate cancer follow-up period.

**Methods:**

MIND-P is a multi-institutional prospective cohort study recruiting newly diagnosed prostate cancer patients for 12-month follow up. It will aim to recruit a final sample of 300 participants undergoing one of four treatment options: active surveillance, radical prostatectomy, radical radiotherapy, or hormone monotherapy. Questionnaire-based data collection consists of multiple validated mental, physical, and social wellbeing outcomes at baseline and 3-monthly intervals until study completion. Primary analysis will include evaluation of treatment undergone against multiple mental wellbeing outcomes. Secondary analysis will additionally explore multiple patient and oncological prognostic factors of potential importance, along with the cumulative incidence of these outcomes, symptom trajectory and their association with subsequent functional and social outcomes.

**Conclusion:**

This cohort study aims to add to the existing limited literature evaluating significant prognostic factors for multiple mental wellbeing outcomes in newly diagnosed prostate cancer patients. This may be of potential use for guiding future prognosis research and of clinical use for identifying individuals potentially requiring additional surveillance or support during routine cancer follow up.

**Study registration:**

This study was prospectively registered on ClinicalTrials.gov (NCT04647474).

## Introduction

Prostate cancer represents a large global public health problem, accounting for almost 1.4 million new cases yearly and being the second most common cancer diagnosis in men [1]. This large incidence, combined with its increasing survival rates, means that not only are growing numbers being diagnosed, but more men are now living with and beyond their disease [2]. Due to this, there is a growing realisation that living longer, and surviving disease, does not always equate to living well. With this in mind survivorship care in cancer has become an increasingly acknowledged topic with large initiatives globally, including the National Cancer Survivorship Initiative (NCSI) in the United Kingdom and similar programmes across the United States such as from the American Cancer Society (ACS) and the American Society of Clinical Oncology (ASCO) [3, 4].

When considering the impact of disease and treatment on prostate cancer patients long term wellbeing, the physical consequences, including urinary and sexual dysfunction, are well described [5]. However, it is only more recently that the mental wellbeing impact of disease is becoming recognised [6]. Mental health issues, particularly depressive and anxiety symptoms are prevalent in this group affecting an estimated 17% of individuals and translating into high suicidal ideation and mortality [7]. Additionally, other issues outside of pure mental health symptoms appear to be important in these men. This includes fear of cancer recurrence (FCR) or progression which has previously been labelled as one of the most common unmet cancer needs [8]. Along with Prostate-Specific Antigen (PSA) Anxiety, FCR is a prevalent issue in patients with prostate cancer [9]. Furthermore, issues surrounding masculinity, masculine-self-esteem and body image appear important in this population and represent constructs which assess the concept of self-worth representing the view of our body and mind and how it is perceived by others around us [10]. All these issues are of undeniable significance in prostate cancer care, not only in their prevalence, but also on the impact they have on treatment choices, functional outcomes and even mortality [11, 12].

However, within much of the prostate cancer literature, physical outcomes after diagnosis and treatment remains the focus, despite not being the end-all of quality of life for patients [6]. This means that whilst it is clear mental wellbeing is an important factor, less appears to be understood about prognostic factors which are associated with poorer mental wellbeing. Beyond hormone therapy, which has been acknowledged as an important factor for outcomes such as depression, there is little consensus on other patient, oncological or treatment factors which are important in mental wellbeing outcomes [13–15]. This is particularly true for outcomes that fall outside of pure mental health, such as anxiety and depression. Additionally, where evidence does exist, including prognostic factors such as younger age, treatments undergone and oncological stage, this evidence is limited to general cancer populations [16–18]. However, it is not clear whether these translate within the prostate cancer setting, particularly when considering the unique and broad experiences these men have post diagnosis.

A better understanding of these factors is important, allowing for better counselling of patients, identification of those who require closer surveillance and better support to improve patient outcomes and gives targeted investigating causes for future research [19]. Additionally, having a good understanding of prognostic factors is vital when considering candidate predictors to use when developing subsequent multivariable prognostic models which may be subsequently used to risk stratify patients at the outset of follow up [20].

## Study aims

With the current literature deficiencies and limited existing evidence on prognostic factors for mental wellbeing outcomes in prostate cancer, the proposed study is primarily aimed as an exploratory study to further define potential factors of interest [19]. Therefore, the primary aim of the study is to evaluate the association between prostate cancer patients undergoing different management options and subsequent mental wellbeing outcomes in the initial cancer follow-up stage. We hypothesise there to be significant differences between different management groups in view of their varying physical symptom loads and demands. More specifically, that those undergoing hormone monotherapy possess the poorest mental wellbeing outcomes, with those undergoing active surveillance the least.

In addition to this, secondary aims include:

To explore patient and oncological prognostic factors associated with mental wellbeing outcomes in patients with prostate cancer.Define incidence of individual mental wellbeing issues in the first year after diagnosis.Explore trajectory of mental wellbeing symptoms in the first year after diagnosis.Assess the relationship between mental wellbeing symptoms and functional, social wellbeing and general health outcomes.

We hypothesise that several patient factors including age, previous mental health history and comorbidities will be significant prognostic factors for poorer mental wellbeing outcomes, based on existing literature in other cancer groups. Similarly, we hypothesise that oncological factors such as stage at presentation and time since diagnosis will be significantly associated with mental wellbeing. Specifically, for time since diagnosis/ symptom trajectory, we hypothesise a downward trend of symptom severity for symptoms such as depression, anxiety and FCR due to increasing time since original diagnosis and reduced uncertainty present post treatment, whilst an upwards trajectory for body image and masculinity symptoms is expected as treatment related side-effects begin to increase with time. Lastly, in view of the extensive literature linking mind and body outcomes in various urological conditions, we believe those with significant mental wellbeing symptoms will possess poorer functional outcomes at study conclusion.

## Materials and methods

### Study design and setting

The Mental wellbeIng aND quality of life in Prostate cancer (MIND-P) study is a prospective and longitudinal cohort study following newly diagnosed prostate cancer patients for 12 months from diagnosis. MIND-P is a multi-institutional study across eight secondary and tertiary hospital sites across London and the south of the United Kingdom (UK). Participating sites are listed in Table 1. Study recruitment started in January 2021, and we expect that the last participant will finish the study in Spring/Summer 2023.

**Table 1 pone.0284727.t001:** Participating study sites and locations.

Hospital Site	Hospital Trust	Location
King’s College Hospital	King’s College Hospital NHS Foundation Trust	Camberwell, London, UK
Princess Royal University Hospital	King’s College Hospital NHS Foundation Trust	Orpington, UK
Guy’s Hospital	Guy’s and St Thomas’ NHS Foundation Trust	Southwark, London, UK
Charring Cross Hospital	Imperial College Healthcare NHS Foundation Trust	Hammersmith, London, UK
Queen Elizabeth Hospital	Lewisham and Greenwich NHS Trust	Woolwich, London, UK
East Surrey Hospital	Surrey and Sussex Healthcare NHS Foundation Trust	Redhill, UK
Medway Maritime Hospital	Medway NHS Foundation Trust	Gillingham, UK
Bedford Hospital	Bedfordshire Hospitals NHS Foundation Trust	Bedford, UK

### Population

The study population consists of newly diagnosed prostate cancer patients undergoing one of four management options for their disease, including:

Active SurveillanceRadical ProstatectomyRadical RadiotherapyHormone Monotherapy

Full inclusion criteria for the study are:

Adults (>18 years old) males with no limit on upper agePossess a new diagnosis of histologically proven or clinically likely prostate cancer with no limits on grade, stage, or histological type of prostate cancerPost multi-disciplinary team discussion with allocation of a suggested management strategyDue to undergo one of the previously listed management optionsFollow up undertaken by urology, oncology, or mixed uro-oncology teams

Exclusion Criteria for the study are:

Patient has already undergone the allocated intervention
○ Attended second active surveillance follow up○ Post-surgery○ Post first radiotherapy dose○ Received >1 dose (initial dose) of Gonadotropin-releasing hormone agonist/antagonist or more than 3 months of daily tablets.Patients receiving the following managements:
○ Palliative patients on symptom control only○ Patients allocated to watchful waiting○ Initially due to undergo any type of Focal therapy e.g., high intensity focused ultrasound (HIFU)○ Patients receiving adjuvant combination therapy e.g., chemotherapy pre radiotherapy or surgery (with the exclusion of hormone therapy)○ Metastatic patients undergoing chemotherapy alonePatients presenting with recurrence or progression of prostate cancerConcurrent management for another cancer diagnosisRecent admission to an inpatient psychiatric facility within the previous 12 months prior to diagnosis of prostate cancerPatients lacking capacity to consent or undertake in the researchThose unable to complete the required surveys, such as those not able to understand English or those with severe learning disability

### Study procedures

#### Recruitment

Identification of potentially eligible individuals is conducted at one of the participating sites of the study. Suitable patients are screened against inclusion and exclusion criteria through local outpatient clinic lists or multi-disciplinary team meeting lists. Potential participants are subsequently asked if they are interested in participating and if they are happy to be contacted by the research team centrally. If interested, contact details are subsequently passed on and participants receive either paper or electronic study packs, depending on their preference. These contain an extensive participant information sheet along with either a physical, or a link for a consent form (S1 File). Subsequently post receipt of the study pack a member of the research team contacts the individual via telephone to conduct a full informed consenting process using a consenting proforma. If individuals are subsequently happy to participate, they are asked to either complete the physical consent form and return this to the research team using a pre-paid envelope or complete the online consent form. A signed copy is subsequently returned to the individual. Individuals then complete their baseline questionnaires. The full process is summarised in Fig 1. This hybrid and remote consenting process was chosen to ensure minimal contact with participants during the COVID-19 pandemic, whilst allowing for access to those without the ability or desire to conduct this electronically

**Fig 1 pone.0284727.g001:**
[figure not shown]
Participant recruitment and consenting procedure overview.

## Data collection and outcomes

This questionnaire-based study is conducted remotely, with no physical follow ups within a hospital site. Again, this design was selected to minimise patient risk during the COVID-19 pandemic. Recruited individuals are asked to complete a series of online or postal questionnaires depending on participant preference (S2 File). Participants are requested to complete the same questionnaire containing a battery of validated mental, physical, and social wellbeing measures at baseline, 3-, 6-, 9-, and 12-months (Fig 2). In addition, at baseline participants are requested to complete some demographic information. Reminders are sent to participants at two- and four-weeks post questionnaire dates if not received within this time frame. Participants are then assumed to be no longer interested in participation and marked as lost to follow up if not returned thereafter. Clinical data extraction is also conducted by the research team to collect baseline disease characteristics and subsequent clinical outcomes. A full list of variables to be collected and analysed as exposure/independent variables are included in Table 2. End of study participation will be at 12 months upon completion of the final questionnaire.

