### Statistical analysis

Descriptive statistics will be calculated for the study population and individual study outcomes. Important definitions to be utilised throughout the data analysis are the threshold set for significant mental wellbeing symptoms in each of the measures collected. For depressive or anxiety symptoms a score of 10 or greater on the PHQ-9 or GAD 7 scales will be used for depression and anxiety respectively, representing moderate symptoms and has been demonstrated to correlate well to depressive or anxiety disorders diagnoses [23, 27]. For the FCR7 scale, a value of 17 or greater was selected, being representative of moderate fear of recurrence/progression as per the tool’s original development [24]. For the BIS, a cut of 10 or greater was selected as a previously demonstrated useful clinically relevant cut off point [28]. Finally, no clear-cut offs exist for the PC-QOL masculine self-esteem subset specifically. However, previously the tool authors have utilised scores of less than 60 to signify a low score for other subsets of the scale, and hence this was selected for this study [29].

Missing data during study follow-up through participant loss to follow up is expected, impacting subsequent analyses for primary and secondary outcomes. Where possible, multiple imputation will be considered for missing outcome data, with complete case analysis to be used for analyses where this is not possible.

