### Primary outcome

Along with the primary objective, the primary study outcome will be the unadjusted mean differences between different management groups of each individual mental wellbeing outcome at 3-, 6-, 9- and 12-months post diagnosis. For this a one-way ANOVA between treatment groups, is planned at each time frame. Subsequent Tukey’s Honest Significant Difference post-hoc analysis will be conducted on any means identified to be statistically significantly different.

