### Secondary outcomes

The following outcomes are not accounted for within the sample size calculations and are therefore considered exploratory. Each planned analysis will be divided per secondary aim of the study.

For exploration of prognostic factors of mental wellbeing outcomes, baseline patient, oncological and treatment factors previously described will be evaluated against the binary outcome of the development of significant individual mental wellbeing symptoms during study follow up. For this analysis an initial univariable, followed by a multivariable regression analysis of potentially significant individual prognostic factors is planned.The cumulative incidence of developing significant individual mental wellbeing outcomes during the 12-month study follow up will be calculated and presented as a percentage.To evaluate the trajectory of mental wellbeing symptoms over a 12-month period and effect of time on symptom scores, mental wellbeing outcome scores of whole cohort and individual treatment cohorts will be evaluated at each follow up time. Evaluation of these scores will be conducted using multilevel mixed-effects analyses to account for the effect of recruitment site clustering and expected loss to follow up during the study.The relationship between each individual mental wellbeing symptom and functional, social, and general health outcomes will be evaluated. Functional outcomes will include sexual, urinary and bowel symptoms from EPIC-26. Social wellbeing will include FACT-G subscale scores with general health defined using the SF-12 physical component score. All outcomes will be evaluated at 12-months. For this each mental wellbeing symptom will be continuously evaluated against these outcomes using univariable and subsequent multivariable linear regression, adjusted for known factors for functional and social outcomes.

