### Sample size

Target sample size calculations are based on the primary aim and outcome of the study evaluating mean differences between different treatment cohorts. This was conducted for hypothesis testing against minimal clinically significant difference (MCSD) of the five mental wellbeing measures of interest, as previously reported in the literature. This was calculated utilising a one-way ANOVA across the four cohorts. Common standard deviation (SD) derived from the literature, or previous pilot data from a small cross-sectional sample were also used to subsequently calculate the effect size f value, with a power of 0.8 and an alpha value of 0.05 utilised. G*Power Software V3.1 [30] was used to calculate the required sample sizes. The largest required sample size across the five mental wellbeing measures was used as the required minimal sample size.

PHQ-9 –MCSD of 5 [31], SD of 3.49 (pilot data)GAD 7 –MCSD of 5 [32], SD of 3.49 (pilot data)FCR7 –MCSD of 10, SD 7.01 [24]BIS–No clear MCSD published in literature [33], use of 10 as cut off for significant symptoms [25], SD of 3.93 (pilot data)Masculine Self-Esteem MCSD of 9.8 [34], SD of 15.79 [35]

Sample size calculations utilising the above values revealed a maximum requirement of 232 participants (58 per cohort) using the PC-QOL Masculine Self-Esteem Scale. Assuming a reasonable dropout rate of 25%, a requirement of 75 participants per cohort was set to give an overall target sample of 300 participants. During recruitment, individual treatment cohorts of these sizes will be targeted, with a gradual stop in recruitment across these different cohorts to gain sizes of groups as close to equal as possible. However, due to likely unequal dropout rates and some crossover to different treatment arms during follow up (e.g. those undergoing surveillance subsequently undergoing radical treatment) it is likely some disparity in cohort sizes will exist. These would subsequently require consideration within analysis and conclusions drawn from study results if any individual cohort contains fewer than the minimum sample size described above.

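### As written, one questionnaire unreturned after two reminders marks a man lost to follow-up, which can turn an occasional miss into permanent dropout.

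*Protocol article*

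**What the plan says.** The protocol article, under Data collection and outcomes, plans the same questionnaire at baseline and at 3, 6, 9 and 12 months, online or by post, with no hospital visits. On late returns it says: "Reminders are sent to participants at two- and four-weeks post questionnaire dates if not received within this time frame". The next sentence is the rule at issue: "Participants are then assumed to be no longer interested in participation and marked as lost to follow up if not returned thereafter".

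Three other places bear on it:

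- **Primary outcome.** The five mental wellbeing scores are compared separately at each of the four follow-up times: "For this a one-way ANOVA between treatment groups, is planned at each time frame".
- **Statistical analysis.** Loss to follow-up is foreseen: "Missing data during study follow-up through participant loss to follow up is expected, impacting subsequent analyses for primary and secondary outcomes". The remedy is conditional: "Where possible, multiple imputation will be considered for missing outcome data, with complete case analysis to be used for analyses where this is not possible".
- **Secondary outcomes.** The trajectory aim alone uses "multilevel mixed-effects analyses to account for the effect of recruitment site clustering and expected loss to follow up during the study".

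Under Sample size, the minimum is 232 men (58 per cohort). A 25% dropout allowance leads to a target of 300, and unequal dropout between cohorts is expected.

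**The concern.** Not returning a questionnaire is not the same as withdrawing. The rule treats the two alike: after two reminders the man is presumed to have lost interest. It applies at any questionnaire date. It does not require a second miss, failed contact or an expressed wish to stop, and no later questionnaire or re-entry is described for him.

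All five primary outcomes come only from these questionnaires, so clinical data extraction cannot replace them. A man who misses month 3 but would have answered later drops out of the 6-, 9- and 12-month comparisons as well. His later scores, which could inform imputation of the missed one and contribute to the mixed model, are never collected. If men miss a questionnaire because of low mood or a treatment course, the permanent exclusion could also shift the cohort means.

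**Working it through.** **Inputs from the article.** Four follow-up waves; target 300; minimum evaluable sample 232; 25% dropout allowance; Masculine Self-Esteem difference 9.8 and SD 15.79; alpha 0.05; power 0.80.

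**Assumed, because the article gives no figure.** A non-return rate p per wave (5%, 7% and 10% shown) after both reminders, with baseline returned by all.

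**Step 1: the plan's own figure.** Take a one-way ANOVA with four groups, two extreme means 9.8 apart and the other two at the midpoint. Then f = (9.8/15.79) × √(1/8) = 0.2194, and the noncentral F gives N = 232 with power 0.803. The stated minimum reproduces.

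**Step 2: what continued sending can recover.** The gain at a wave is the number of men who missed an earlier wave but would return this one. It cannot be negative, provided further mailings do not themselves drive men away. If no man who misses would ever return, it is zero.

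**Step 3: the independent-miss case.** With p the same at every wave, the share available at wave j is (1 − p)^j if a miss is final and 1 − p if sending continues. Positive clustering within men makes the gap smaller, so this is the upper end. Men available out of 300:

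| p | Miss final: 3 mo | 6 mo | 9 mo | 12 mo | Sending continues: any wave |
|---|---|---|---|---|---|
| 5% | 285 | 271 | 257 | 244 | 285 |
| 7% | 279 | 259 | 241 | 224 | 279 |
| 10% | 270 | 243 | 219 | 197 | 270 |

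For example, at 7%: 300 × 0.93^4 = 224, against 300 × 0.93 = 279. At 3 months the two columns agree, because no earlier follow-up wave can have been missed.

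**Step 4: power at 12 months.** This uses the f of Step 1, near-equal cohorts and no imputation.

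- p = 5%: 0.825 if a miss is final, 0.885 if sending continues
- p = 6.9%: 0.787 against 0.878
- p = 10%: 0.724 against 0.865

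The 6.9% rate is the one at which independent, final misses produce 25% loss over four waves: 1 − 0.75^(1/4) = 0.069.

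**Step 5: bias, as an illustration only.** Suppose 17% of men are symptomatic throughout (the Introduction's prevalence estimate), with assumed non-return of 10% per wave if symptomatic and 5% if not. Prevalence among 12-month responders is then:

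- miss final: 0.17 × 0.90^4 / (0.17 × 0.90^4 + 0.83 × 0.95^4) = 14.2%
- sending continues: 0.17 × 0.90 / (0.17 × 0.90 + 0.83 × 0.95) = 16.3%

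Under these invented rates the rule enlarges the distortion. Continued sending reduces it without removing it.

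**The case against.** **The text does not literally say that mailings stop.** It sets no deadline for a late return, and an article condenses a fuller protocol that may deal with re-contact. This stands as a limit on certainty. But the sentence is a stated rule, not a gap. A presumption of lost interest together with lost-to-follow-up status naturally means that follow-up ends, and nothing in the article says otherwise.

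**The figures are an upper end.** If non-response is persistent, as the rule itself presumes, continued sending recovers few or no men. This stands, and the size must be given as a range from zero. The loss is also uneven over time: at 7% the counts at 6 and 9 months (259 and 241) remain above 232, and only the 12-month count falls below it.

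**The analysis already has mitigations.** Multiple imputation and the mixed model are foreseen. Both help, but in standard form they rely on missingness at random. Imputation is only to be considered, with complete cases as the fallback, and the mixed model serves a secondary aim. Both would also work better with the later scores.

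**Limiting contact is defensible in a remote study of sensitive topics.** That supports stopping reminders for one wave. It does not require one miss to be final, since men can still withdraw at any time.

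**Two stronger readings are not supported.** A reader might infer that the rule biases cohort means towards well men. The article expects unequal dropout between cohorts but does not link dropout to distress, so the bias is plausible and unproven. A reader might also infer that the rule exhausts the 25% allowance. That allowance may already include men marked lost in this way. Whether 300 covers 232 after 25% loss (300 × 0.75 = 225) is a separate sample-size question.

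**Conclusion.** The point holds as an avoidable loss of primary outcome data that is cheap to prevent. Read naturally, the rule makes a single miss permanent although the man has not withdrawn. It can reduce evaluable numbers at 6, 9 and 12 months, but not at 3 months, and it withholds later scores from imputation and the mixed model.

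The 12-month gain from continued sending lies between zero and, with independent misses, 41 men at 5% (285 − 244), 55 at 7% (279 − 224) and 73 at 10% (270 − 197), out of 300. The rates and the independence are assumptions; observed return patterns would place the study within the range. Added bias is a possibility that the article suggests only indirectly.

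**What to change.** Replace the rule under Data collection and outcomes as follows:

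- Record a questionnaire still unreturned after the two reminders as a missed wave.
- Keep sending later questionnaires through month 12 unless the man withdraws or dies.
- Reserve lost to follow-up for withdrawal, loss of contact or no return at 12 months, and report non-return separately from withdrawal.
- Include scores from men with intermittent gaps in the imputation for the per-visit ANOVAs, and in the mixed model.

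If the full protocol already provides for continued sending, correcting the sentence is enough.

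The cost is some extra postage or e-mails and possibly a minor amendment. Recruitment began in January 2021, so a change would put earlier and later participants under different follow-up rules. The date of the change should be reported, with return rates before and after it.
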